**Methods/Design:**

In a randomized controlled trial, one group will receive a maximal intervention (= intervention group). The intervention group will be compared to the control group receiving a minimal intervention. An inclusion of 350 patients in total, with a follow-up of 3 years is foreseen. The inclusion criteria are age between 25–65 and insured by the Onderlinge Ziekenkas, insuring for guaranteed income in case of illness for self-employed. The maximal intervention group receives several prevention consultations by their general practitioner (GP) using a new type of cardiovascular risk calculator with personalised feedback on behavioural risk factors. These patients receive a follow-up with intensive support of health behaviour change via different methods, i.e. a tailored website and personal advice of a multidisciplinary team (psychologist, physiotherapist and dietician). The aim of this strategy is to reduce cardiovascular risk factors according to the guidelines. The primary outcome measures will be cardiovascular risk factors. The secondary outcome measures are cardiovascular events, quality of life, costs and incremental cost effectiveness ratios. The control group receives prevention consultations using a new type of cardiovascular risk calculator and general feedback.

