#### Primary aims

1. To examine the effects of medical and behavioural interventions on medical parameters such as systolic blood pressure, diastolic blood pressure, total blood cholesterol level, blood glucose level (HbA1c), overweight and obesity, BMI.

2. To examine the effects of medical and behavioural interventions on health related behaviour such as physical activity; fat; fruit and vegetable intake; and smoking behaviour.

3. To examine the effects of medical and behavioural interventions on overall cardiovascular risk mediated by changes in medical and/or behavioural risk factors.

4. To determine the proportion study participants with a 10% reduction in systolic blood pressure with participants with hypertension

5. To determine the proportion study participants with a 10% reduction in diastolic blood pressure with participants with hypertension

6. To determine the proportion study participants with a 10% reduction in total cholesterol with patients with hypercholesterol

7. To determine the proportion study participants with a 10% reduction in HB1Ac with initial HB1Ac >7% (high risk)?

8. To determine the proportion study participants with a 10% reduction in weight with initial BMI >25 kg/m^2^?

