### Analysis and power

A power calculation was performed to determine the number of study participants needed to detect a significant effect of the PreCardio prevention programme. A t-test will be used to compare the means of the outcome measures from the intervention and the control group. The sample size calculation is based on the population standard deviation of the primary outcome measure. For PreCardio, this is, for instance, systolic blood pressure. Kelley *et al *found a mean systolic blood pressure of 125 mm/Hg (SD 14 mm/Hg)[42]. The sample size calculation was performed with Nquery Advisor 4.0^®^. A two group t-test with a 0,05 two-sided significance level will have 82% power to detect the difference between a Group 1 mean of 120 mm/Hg and a Group 2 mean of 125 mm/Hg, a difference in means of -5 mm/Hg, assuming that the common standard deviation is 14 mm/Hg, when the sample sizes in the two groups are 200 and 100, respectively (a total sample size of 300). Other outcome measures were also used to determine the necessary sample size. A recent study about the effect of a computer-tailored intervention to reduce fat intake included at post-test a mean fat intake of 85 grams/day (SD 34.5 grams/day) [43]. A two group t-test with a 0,050 two-sided significance level will have 80% power to detect the difference between a Group 1 mean of 85 grams/day and a Group 2 mean of 97 grams/day, a difference in means of -12 grams/day assuming that the common standard deviation is 34.5 grams/day, when the sample sizes in the two groups are 200 and 100, respectively (a total sample size of 300). Another study evaluating a website-delivered computer-tailored intervention for increasing physical activity increased physical activity with a mean of 77 minutes in the intervention group [44]. In this study the total moderate- and vigorous-intensity physical activity was chosen as an outcome measure. This measure can be used to determine the necessary sample size to detect a difference in means in the present study. At follow up this measure had a mean of 363 minutes (SD 323) for the intervention group and 241 minutes (SD 269) for the control group [43]. A two group t-test with a 0,05 two-sided significance level will have 86% power to detect the difference between a Group 1 mean of 363 minutes and a Group 2 mean of 241 minutes, a difference in means of 122 minutes, assuming that the common standard deviation is 323 minutes, when the sample sizes in the two groups are 200 and 100, respectively (a total sample size of 300).

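### No single primary outcome or assessment time is fixed, and three outcomes are each sized at an unadjusted two-sided 0.05

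*Protocol article*

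**What the plan says.** All references are to the protocol article.

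- **Abstract, Methods/Design.** A whole class of outcomes is primary: "The primary outcome measures will be cardiovascular risk factors".
- **Primary aims.** There are eight. Aim 1 covers "medical parameters such as systolic blood pressure, diastolic blood pressure, total blood cholesterol level, blood glucose level (HbA1c), overweight and obesity, BMI". Aim 2 covers "health related behaviour such as physical activity; fat; fruit and vegetable intake; and smoking behaviour". Aim 3 is "overall cardiovascular risk mediated by changes in medical and/or behavioural risk factors". Aims 4 to 8 are five responder proportions, the first of which reads "To determine the proportion study participants with a 10% reduction in systolic blood pressure with participants with hypertension". The lists in aims 1 and 2 are worded as examples, so they are not closed.
- **Analysis and power, sample size.** The calculation is said to rest on the primary outcome measure, in the singular, and then: "For PreCardio, this is, for instance, systolic blood pressure". Next comes "Other outcome measures were also used to determine the necessary sample size", with separate calculations for fat intake and physical activity. All three use a two-sided 0.05 and groups of 200 and 100. The stated powers are 82%, 80% and 86%. No visit is given for any of them.
- **Analysis and power, last paragraph.** A linear regression is planned for the change in overall cardiovascular risk from baseline to 3 years. No power calculation is given for it.
- **Study measurements, Table 1.** After baseline, the GP-measured factors are scheduled for everyone at 12, 24 and 36 months, with 4 and 8 months depending on risk. The behaviours are scheduled at 6, 12, 18, 24, 30 and 36 months.

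**The concern.** The three places that define the primary outcome disagree: the abstract gives a class, the aims give a long open list, and the power section gives one measure that is only an example. The outcomes that are sized have no time, and the one outcome that has a time is not sized.

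Each quoted power belongs to one outcome tested alone at 0.05. With three outcomes sized in this way and many more called primary, the text does not say which comparison carries the 5% error rate. The outcome and visit on which the programme is judged could therefore be settled after results are known. Splitting the error rate would protect against that, but then the stated powers would no longer hold.

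**Working it through.** **1. Reproduce the stated power.** Inputs are from Analysis and power: n = 200 and 100, two-sided 0.05. Standard error = SD × √(1/200 + 1/100) = SD × 0.12247. Noncentrality = difference / standard error. Power is from the noncentral t with 298 degrees of freedom.

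| Outcome | Difference | SD | Standard error | Noncentrality | Power found | Power stated |
|---|---|---|---|---|---|---|
| SBP (mmHg) | 5 | 14 | 1.715 | 2.916 | 82.8% | 82% |
| Fat intake (g/day) | 12 | 34.5 | 4.225 | 2.840 | 80.8% | 80% |
| Physical activity (min) | 122 | 323 | 39.56 | 3.084 | 86.7% | 86% |

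The stated figures reproduce to within a percentage point. The arithmetic is sound; the open question is which test it belongs to.

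**2. Count the primary outcomes.** Aim 1 has 6, aim 2 has 4 (fruit and vegetables taken together), aim 3 has 1 and aims 4 to 8 have 5: 6 + 4 + 1 + 5 = 16. Overweight/obesity overlaps with BMI, and the five responder proportions re-express SBP, diastolic pressure, cholesterol, HbA1c and weight. Removing these leaves 16 − 1 − 5 = 10 distinct measures.

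**3. Family-wise error under a conditional rule.** Suppose each outcome is tested once between the arms at 0.05, any one significant result counts as success, and the programme has no effect on anything. With independent tests the chance of at least one false positive is 1 − 0.95^m. With correlated tests it was computed for jointly normal test statistics with one common correlation. The article gives no correlations, so these are assumptions.

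| Outcomes tested (m) | Correlation 0 | 0.3 | 0.5 | 0.7 |
|---|---|---|---|---|
| 3 (those sized) | 14% | 14% | 13% | 11% |
| 10 (distinct measures) | 40% | 35% | 29% | 21% |
| 16 (all listed) | 56% | 48% | 37% | 26% |

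Each row is for a single visit.

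**4. What adjustment would cost.** With the three sized outcomes each tested at 0.05/3 = 0.0167, the noncentral t gives:

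| Outcome | 200/100 at 0.05 | 200/100 at 0.0167 | 233/117 at 0.0167 |
|---|---|---|---|
| SBP | 82.8% | 69.4% | 77.2% |
| Fat intake | 80.8% | 66.7% | 74.6% |
| Physical activity | 86.7% | 75.0% | 82.3% |

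The last column takes all 350 planned participants at 2:1 as analysed. It is an upper bound, since any dropout over 3 years lowers it.

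**The case against.** The strongest reply has four parts.

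- **A multiplicity method may sit in an analysis plan that is not shown.** This stands as far as the method goes, and its absence is not the point here. Choosing the primary outcome is a protocol decision, however. The article makes that choice in three places and they do not agree. A later plan also cannot restore power figures that already give each of three outcomes a full 0.05.
- **The article never says that one significant outcome is enough.** This stands. A reader might infer that the programme may be declared effective on whichever risk factor reaches significance, but no sentence states such a rule. The error rates above are therefore conditional.
- **Sixteen overstates the family.** This stands in part. Several items overlap, and aims 4 to 8 ask for proportions without stating a between-arm test. That is why 10 and 3 are shown as well. Even three outcomes give more than twice the nominal 5%.
- **The timing is not wholly open.** This stands. A reader might count nine possible visits from Table 1, but one is baseline and no outcome is scheduled for everyone at all nine. Overall cardiovascular risk does have a model and a 3-year horizon. SBP is thus the natural choice from the sizing, but not the only one the sponsor could defend.

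**Conclusion.** The point holds: the article does not fix one primary outcome and time, and its stated power of 80–86% goes with a 5% error rate only if a single outcome is primary. This should be corrected before the data are seen.

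The size depends on a success rule that the article does not state. If any one result at 0.05 sufficed, the family-wise error with no true effect would be 11–14% for the three sized outcomes, 21–40% for 10 distinct measures and 26–56% for all 16. The low end of each range assumes a common correlation of 0.7 and the high end independence.

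A reader might turn the upper figures into a claim that a positive trial would have about a 50% chance of being false. The documents do not support that. The figures are the chance of at least one significant result when the programme does nothing. The chance that a positive result is false depends also on the prior probability of an effect and on power.

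**What to change.** Reconcile the abstract, the Primary aims section and both parts of Analysis and power:

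1. Name one primary outcome and one time, before the data are seen. The between-arm difference in SBP at 36 months, two-sided 0.05, is one option that the first power calculation already supports. If overall cardiovascular risk at 3 years is chosen instead, give it its own power calculation.
2. Delete the wording in Analysis and power that presents the primary outcome as an example, and present the fat intake and physical activity calculations as supporting information on secondary outcomes.
3. Move the remaining items of aims 1 to 8, including the responder proportions, to secondary. Test them by Holm or in a fixed order, or report estimates with confidence intervals and no claim of significance.

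The cost is wording only: no extra participants and no new data, and with SBP the stated 82% power stands. The downside is that results on the other risk factors can no longer be called primary. If the sponsor prefers to keep three co-equal outcomes at 0.05/3, the article should state the lower power that goes with that choice.

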## Methods/Design

### Study population

PreCardio is a randomized controlled trial. Approval was obtained from the ethics committee of the University Hasselt. A total of 350 subjects will be included in the study with a follow-up of 3 years. The inclusion criteria are age between 25–65 and insured by the Onderlinge Ziekenkas, insuring for guaranteed income in case of illness for self-employed. All study participants need to sign an informed consent and have access to the internet. Other eligitability criteria are not included.

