#### Cardiovascular risk assessment

Cardiovascular risk assessment will be based on the SCORE risk table (Fig 3) [15]. The overall cardiovascular risk score is the 10-year risk to die from CVD. According to SCORE a risk score of 4% or more is considered a high risk. A risk score in the range 2%–4% is considered a medium risk and a score lower than 2% is seen as a low risk[3]. The medical and behavioural advices following risk assessment are adapted from the Boland algorithm[16]. Cardiovascular risk assessment in the PreCardio-study is thus an adaptation of existing and validated risk assessment flowcharts in Belgium (Fig 2).

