### Interventions

#### Minimal intervention

##### Medical prevention consultation

The interventions targeted on medical parameters include a first medical prevention consultation with the GP. In this medical prevention consultation the cardiovascular risk (risk on having a heart attack in the next 10 years) will be calculated using a new computer programme. This computer programme is called "Electronic Prevention Record" (EPR). Innovative about the EPR is its connection to "Electronic Medical Record" (EMR). The EMR is also a computer programme, a record about the medical history and treatment provided to the patient. In the province of Limburg, the setting for the PreCardio-study, 75% of the GPs use an EMR[36]. In Belgium, 70% of the GPs use an EMR [37]. In Belgium there are 17 different providers of EMRs. The EPR generates, after a limited input (thanks to the connection to the EMR), the cardiovascular risk, the therapeutic goals (targeted on medical parameters and behaviour change) and a target date for the next follow-up consultation. This date is dependent on the determined cardiovascular risk. During these medical prevention consultations medical practice will be performed: measurement (e.g. blood pressure) and installation of treatment to influence medical parameters. Supplementary, the GP performs stage of change assessment (Table 2) using the EPR. The GP asks for PA and diet which statement fits the participant's situation best. If it is a smoker, the stage of change for quitting smoking is assessed as well. The stage of change assessment is for the control group not followed by tailored feedback for behaviour change.

All data collected at the medical prevention consultation are stored in the EPR that is connected to the EMR (Fig 4). Therapeutic goals in line with cardiovascular risk are determined. These goals, together with the data provided by the study participant are electronically sent to the study office by a secured connection. The information from the intervention group is closely examined and the participants of the intervention group will receive a reminder from the study office when it is time to plan their next medical prevention consultation.

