
A linear regression model will be employed to assess the effects of the prevention programme on change in overall cardiovascular risk from baseline to 3 year follow-up.

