## Discussion

The PreCardio-study is a randomized controlled trial. However, the shared worksite setting could lead to an intervention contamination. In this regard, the failure to find significant effects from the Heartbeat Wales programme due to contamination of the reference area is relevant[38]. Partially, this study is similar to the PreCardio-study since it compares the effects of a multiple risk factor intervention. However, the multiple risk factor intervention from the "Heartbeat Wales" programme was less individually tailored, didn't include GPs as key figures, offered no multidisciplinary support and made no use of modern information technology like a personalised website for participants of the study. The benefits of these interventions targeted at behavioural risk factors could be substantial. After all, the PREMIER study, a clinical trial of comprehensive lifestyle modification for blood pressure control, was already effective in reducing cardiovascular disease risk [49]. This study is similar to the PreCardio-study because it targets one of the medical risk factors for cardiovascular disease. However, in the present study other risk factors will be targeted as well leading to a reduction in the overall cardiovascular risk.

Several aspects of the PreCardio-study are noteworthy. Firstly, all interventions are based on recent guidelines and knowledge on CVD prevention. Moreover, this knowledge was taken as a basis to develop a new computer programme for GPs. After limited input, this programme automatically determines CVD risk and generates therapeutic goals according to this risk. Furthermore, tailored advice is provided to the study participant. The involvement of GPs in the PreCardio-study is paramount. Secondly, study participants are provided with a number of aids to support them with behaviour change. These include a personalised website with tailored feedback and personal support from a multidisciplinary team. Consequently, a reduction in medical and behavioural risk factors resulting in a reduction in overall CVD risk is expected.

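### The 3-year change in SCORE risk carries ageing into primary aim 3: no bias between arms, but precision is lost unless age is fixed or adjusted for

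*Protocol article*

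**What the plan says.** All references are to the protocol article.

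- **Outcome.** Under *Primary aims*, the third aim is the effect on overall cardiovascular risk as mediated by changes in medical or behavioural risk factors. *Cardiovascular risk assessment* defines the measure: "The overall cardiovascular risk score is the 10-year risk to die from CVD". It adds that "a score lower than 2% is seen as a low risk".
- **Analysis.** *Analysis and power* gives one sentence: a linear regression model for the programme's effects, with the outcome "change in overall cardiovascular risk from baseline to 3 year follow-up". It names no scale (absolute, relative or log), no covariates and no handling of age.
- **Population.** *Study population*: "The inclusion criteria are age between 25–65", plus membership of one insurer, consent and internet access. "Other eligitability criteria are not included", so there is no risk threshold.
- **Expectation.** *Discussion*: "a reduction in medical and behavioural risk factors resulting in a reduction in overall CVD risk is expected".
- **Power.** *Analysis and power* gives effect sizes and power for systolic blood pressure, fat intake and physical activity, and none for overall risk.

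A side point: *Medical prevention consultation* describes the calculated risk as the "risk on having a heart attack in the next 10 years", which does not match the definition as a risk of cardiovascular death. The argument below uses the latter.

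**The concern.** Aim 3 asks what the programme does through blood pressure, cholesterol, smoking and similar factors. Ageing is none of these. If the score rises with age, each participant's 3-year change is the sum of a modifiable part and an ageing part. On the absolute scale the ageing part is roughly proportional to baseline risk. It is therefore small in the young and large in the old, and the 25–65 age range makes it very uneven.

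Two things are at stake. The first is precision: uneven ageing spreads out the change scores in both arms and widens the confidence interval for the programme effect. The second is interpretation: with a modest benefit the intervention-arm mean would still go up, and someone looking for a fall within that arm could misread a working programme as a failure.

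**Working it through.** **1. The plan's own power figures.** With 200 and 100 per arm, √(1/200 + 1/100) = 0.1225 and the standard error is SD × 0.1225.

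| Outcome | Difference / SE | Power, normal / t | Stated |
|---|---|---|---|
| Systolic pressure | 5 / (14 × 0.1225) = 2.92 | 83.1% / 82.8% | 82% |
| Fat intake | 12 / (34.5 × 0.1225) = 2.84 | 81.1% / 80.8% | 80% |
| Physical activity | 122 / (323 × 0.1225) = 3.08 | 87.0% / 86.7% | 86% |

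These reproduce within 2 points. None of them concerns overall risk.

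**2. Ageing alone.** Assumption: risk doubles every *d* years of age, *d* = 6 to 10. Three years multiply risk by 2^(3/d), and the relative cut needed just to stand still is 1 − 2^(−3/d).

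| d | Rise over 3 years | Break-even cut |
|---|---|---|
| 6 | 41% | 29% |
| 7.5 | 32% | 24% |
| 10 | 23% | 19% |

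A second set of assumptions (growth of 8–13% per year) gives break-even cuts of about 21–32%.

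**3. Two participants at d = 7.5 (factor 1.32) and a 10% relative effect.**

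- Baseline 1%: control 1.32 (+0.32 points); intervention 1.32 × 0.9 = 1.19 (+0.19).
- Baseline 4%: control 5.28 (+1.28); intervention 5.28 × 0.9 = 4.75 (+0.75).

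Both intervention participants rise although the programme works. The benefit is visible only against control (−0.13 and −0.53 points). The ageing term differs fourfold between the two people.

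**4. Simulation of the trial.** All inputs are assumed except the 2:1 allocation, the 200/100 split and the age limits: ages uniform over 25–65, risk 1% at age 45, log-SD 0.4 between people, within-person log-SD 0.25 over follow-up.

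- *No effect:* the arm means rise equally (for example +1.07 and +1.07 points at d = 6), and the regression rejects in 4–6% of runs. There is no bias.
- *10% effect:* the intervention-arm mean rises by 0.2 to 0.7 points, and 66–83% of that arm show an increase. At 20% the mean is still +0.02 to +0.40.
- *Where the variance sits:* participants over 55, a quarter of the sample, supply 70–81% of the control-arm variance. Of all participants, 65–75% start below 2%.

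Power for a 10% effect (1,500 runs):

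| Analysis | d = 6 | 7.5 | 10 |
|---|---|---|---|
| Raw absolute change | 39% | 49% | 62% |
| Same, adjusted for baseline risk and age | 57% | 62% | 69% |
| Absolute change, age fixed at baseline | 57% | 62% | 70% |
| Log ratio, observed age | 94% | 93% | 93% |
| Log ratio, age fixed | 94% | 93% | 93% |

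Repeat runs move these by a few points, hence the ranges 35–63% and 55–71%. For a 20% effect, raw-change power is 94%, 98% and 100%.

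**5. Wider assumptions.** A second model used growth of 8–13% per year, median risk of 3% or 5% at age 65, and within-person log-SD 0.15–0.40. At a 10% effect, raw change had 16–83% power and adjusted change 22–96%. At 20%, raw change had 60–100%.

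**6. Rounding.** In the second model with 10% growth and 3% risk at age 65, rounding scores to whole percents at a 10% effect cut adjusted and age-fixed power from about 55–58% to about a third.

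**The case against.** The strongest reply is that this is a randomised comparison. The regression is meant to estimate the programme's effect, the control arm ages just as much, and the drift cancels in expectation. That is correct, and step 4 confirms it. A reader might infer that ageing swamps the programme's effect; the documents do not support that.

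A reader might also infer that the expected reduction would usually fail to appear. That sentence sits in the *Discussion*, is not an endpoint or success criterion, and reads naturally as a reduction relative to control.

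A third tempting reading sets the 35–63% power of raw change against the 92–94% of a log ratio and blames ageing for the gap. The last two table rows refute this: on the log scale, fixing age changes nothing, because in this model ageing multiplies everyone's risk by the same constant. Nearly all of that gain is the change of scale. The log scale is also debatable as a target, since it gives a relative change in a very-low-risk 30-year-old the same weight as one in a 60-year-old, whereas the article classifies risk in absolute bands.

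It is also fair to say that an absolute, unadjusted change is only the plain reading of one sentence in a condensed article, and that scale and covariates may be set in a fuller plan. This limits the weight of the point. What stands is that outcome, time window and model are stated here, the outcome as defined contains ageing, and the aim is about modifiable factors.

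**Conclusion.** The point holds as a matter of precision and interpretation, not of validity. Read plainly, the analysis of primary aim 3 leaves three years of ageing in the outcome. The between-arm estimate remains unbiased. For a 10% relative effect, age-fixing or adjustment raises power by roughly 10 to 20 percentage points (from about 35–63% to about 55–71%). For a 20% effect it matters little in the main model and somewhat more if within-person variation is large. For effects below the break-even cut of about 19–32%, mean scores would rise in both arms.

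Every one of these sizes depends on the assumed age slope, risk level, variability and effect. The SCORE table is not shown, and the documents state no expected effect on overall risk. The direction needs only that the score rises with age. This is a cheap improvement, not a flaw that endangers the trial.

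**What to change.** - For aim 3, compute the 3-year score from the 3-year blood pressure, cholesterol and smoking values at the participant's **baseline age**, using the unrounded score. Alternatively, keep the observed-age score and enter baseline risk and age as covariates in the linear regression. In the main model the two perform about equally.
- State that the programme effect is the between-arm difference.
- Report the observed-age absolute change alongside it.
- Word the expectation in the *Discussion* as a lower risk than in the control group.
- A log-ratio analysis may be added as a sensitivity analysis. It is a choice of scale, not a correction.
- When editing, reconcile the two descriptions of the calculated risk (cardiovascular death; heart attack).

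**Cost.** A sentence or two in *Analysis and power*, a rewording in the *Discussion* and a recalculation. *Table 1* already schedules blood pressure and cholesterol at the GP, and smoking on the website, at 0 and 36 months, so no new measurement is needed. The downside of fixing age is that the main result becomes an age-standardised change and not the risk actually observed at 3 years, which is why both should be shown.
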